## Abstract

**Introduction:**

Young people are the most frequent users of social media and smartphones and there has been an increasing speculation about the potential negative impacts of their use on mental health. This has coincided with a sharp increase in the levels of self-harm in young people. To date, studies researching this potential association are predominantly cross-sectional and reliant on self-report data, which precludes the ability to objectively analyse behaviour over time. This study is one of the first attempts to explore temporal patterns of real-world usage prior to self-harm, to identify whether there are usage patterns associated with an increased risk.

**Methods and analysis:**

To study the mechanisms by which social media and smartphone use underpin self-harm in a clinical sample of young people, the Social media, Smartphone use and Self-harm in Young People (3S-YP) study uses a prospective, observational study design. Up to 600 young people aged 13–25 years old from secondary mental health services will be recruited and followed for up to 6 months. Primary analysis will compare real-world data in the 7 days leading up to a participant or clinician recorded self-harm episode, to categorise patterns of problematic usage. Secondary analyses will explore potential mediating effects of anxiety, depression, sleep disturbance, loneliness and bullying.

**Ethics and dissemination:**

This study was approved by the National Research Ethics Service, London - Riverside, as well as by the Joint Research and Development Office of the Institute of Psychiatry, Psychology and Neuroscience and South London and Maudsley NHS Foundation Trust (SLaM), and the SLaM Clinical Research Interactive Search (CRIS) Oversight Committee. The findings from this study will be disseminated through peer-reviewed scientific journals, conferences, websites, social media and stakeholder engagement activities.

**Trial registration number:**

NCT04601220.

Strengths and limitations of this studyThe Social media, Smartphone use and Self-harm in Young People (3S-YP) study uses a novel prospective, observational strategy to investigate the patterns of real-world social media and smartphone usage prior to episodes of self-harm in a clinical youth sample.Co-production with youth experts by experience, including coauthor ([name]), a leading national UK youth mental health charity—YoungMinds, and a steering group comprising of experts in the field of self-harm and suicide prevention will ensure acceptability and relevance, as well as facilitate dissemination and impact.Due to the online nature of the study, participants need to be able to independently engage with the digital tools and study documentation that is only available in the English language.The flexible approach to participation regarding which data young people choose to share, will ensure our methods are acceptable and promote autonomy among participants, though it will increase the risk of missing and inconsistent data which could compromise the validity of the results and interpretations made.Mixed model analyses, state-of-the-art natural language processing methods combined with thematic analysis, will be used to analyse social media metadata, textual and imagery data and smartphone metadata.

## Introduction

Self-harm is characterised as any behaviour where an individual causes damage or injury to their body in response to distress. Traditionally, research has focused more on severe cases of self-harm, namely cutting or self-poisoning, rather than a broader spectrum of behaviour, including burning, scratching or hitting oneself. Self-harm in young people is a significant public health concern, with findings indicating that more than 15% of the young people report engaging in self-harm in the community, coupled with high rates of repetition and elevated risk of suicide.^1–3^ Prevalence figures are likely to underestimate the true scale of the problem, given young people are often reluctant to disclose and seek professional help owing to fear of stigma.^4^ Furthermore, epidemiological studies tend to rely on hospital presentations and only reflect those cases of self-harm that are brought to medical attention.^5^ Whereas community and school-based studies collect self-reported retrospective data. Therefore, while capturing a wider range of self-harm behaviours, they lack information about the specific timing and nature of non-help seeking self-harm.

Reasons for self-harm are complex and multifaceted, however there has been an increasing speculation about the potential negative impacts of social media and smartphone use on youth mental health.^6^ Young people are the most frequent users of social media and smartphones, with 91% of 12–15 year olds using social media and 98% of 13-year olds owning a smartphone in the UK.^7^ Over the last decade, social media and smartphones have altered how young people spend their time and interact socially with peers.^8^ This coincides with a sharp increase in the levels of self-harm, particularly among adolescent women.^9^ Given the widespread use of social media and smartphones, understanding the implications for youth mental health is of paramount importance.

Social media platforms are often used by people with mental health problems to share personal experiences and seek support.^10^ Feedback received can be perceived as supportive by the individual.^11^ Thus, social media use can alleviate loneliness and social isolation that is common among young people with mental health problems as it can provide opportunities for strengthening existing friendships and developing new social connections, however, it can also exacerbate loneliness if excessive time is spent online rather than time that would be otherwise spent interacting socially offline.^12 13^

Online forums have been a cause for particular concern as users may be exposed to harmful self-harm content and online discussions that normalise behaviours and discourage help-seeking, which may be associated with increased suicidal ideation found among forum users compared with other forms of social media user.^10^ Other studies have found significant associations between cyberbullying victimisation and self-harm in young people, and to a lesser extent, cyberbullying perpetration, likely perpetuated by the anonymous nature of social media.^14^ Young people engaging in self-harm behaviours may also be more likely to engage in risky online behaviour compared with their peers.^15^ More recent findings indicate that while for some young people and in certain circumstances, social media can have a positive or neutral effect, for others it can be harmful and so more research is needed to explore the effects of different types of social media use on an individual level.^16 17^

Research on the effects on mental health of excessive screen time in general is more conflicting, possibly relating to inconsistencies in measurements and definitions employed.^18–20^ Sohn *et al*,^20^ found evidence of an association between problematic smartphone usage and increased anxiety and depression. Emerging evidence indicates that problematic smartphone usage may be positively linked with suicide ideation and the association may be mediated by emotional intelligence.^21 22^ Furthermore, there is an established literature linking excessive smartphone use and sleep disturbance^23^ and poor sleep has been linked to depression and suicidal ideation in young people,^24^ as well as there being an association between sleep problems and suicidal thoughts and behaviours independent of depression.^25^

Much of the current evidence on the association between social media and smartphone use and mental health and self-harm among young people is limited to associations from cross-sectional studies (eg, Mancinelli *et al*).^26^ Where longitudinal studies are reported, they are based on small samples, are reliant on self-report data and have prolonged periods of time between waves of data collection (eg, Arendt *et al*.)^27^ These approaches have precluded the ability to explore potential mechanisms underlying self-harm behaviour over time using real-world data, in a prospective way. This study is one of the first to attempt to explore the temporal patterns of social media and smartphone use prior to episodes of self-reported and clinician-reported self-harm events, to identify whether there are usage patterns of social media and smartphone use that are associated with increased risk of self-harm. The findings from this study have the potential for generating a wide-ranging impact as well as filling the gaps in current knowledge. The overarching aim of the Social media, Smartphone use and Self-harm in Young People (3S-YP) study is to investigate the mechanisms by which social media and smartphone use underpin self-harm in a clinical sample of young people. Primary objectives are:

To identify characteristic patterns of social media and smartphone use in the 7 days preceding an episode of self-harm.To determine whether characteristic patterns of social media and smartphone use associated with an episode of self-harm, differ from young people who have not had an episode of self-harm.

Secondary objectives are to investigate whether the association is mediated by sleep disturbance, depression, anxiety, loneliness and bullying.

## Methods and analysis

### Study design

This study is a prospective 6-month cohort study and has been reported according to the Strengthening the Reporting of Observational Studies in Epidemiology checklist for cohort studies (see online supplemental additional file 1) (protocol V.1.4, 21/07/2022).

10.1136/bmjopen-2022-069748.supp1Supplementary data

### Study setting

Young people (aged 13–25 years) will be recruited from South London and Maudsley NHS Foundation Trust (SLaM). SLaM is one of the largest mental healthcare providers in Europe, providing secondary mental healthcare to a local population of approximately 1.3 million residents as well as national and specialist services.

### Participant selection

Young people will be identified via one of the following selection methods:

SLaM’s Consent for Contact (C4C) patient research participation register of patients who have given prior consent to researchers with ethically approved studies to access their health records and contact them for the purposes of recruitment to research for which they are eligible.^28^ A researcher who is independent of the study team and who works for the National Institute for Health Research Biomedical Research Centre within SLaM, will apply the eligibility criteria to the register using the Clinical Research Interactive Search (CRIS) system to screen for potentially eligible young people. The CRIS system is a case register that contains de-identified information extracted from the Trust’s electronic health record (EHR) system.^29^ The study team will then be supplied with the Trust-identifying details of potentially eligible young people so they can check their EHRs in detail for clinical eligibility. For eligible young people, the study team will inform the care coordinator of the intention to approach prior to initiating any contact. This is so that care coordinators can advise if it is not appropriate for a young person under their care to be approached for the study.If the above yields insufficient numbers, we will invite clinicians to refer young people under their care directly to the study team. We will attend team meetings to explain the study and eligibility criteria to clinicians. Clinicians will screen young people under their care for eligibility and will contact eligible young people (and a parent or carer with parental responsibility for young people aged 13–15 years old) to explain the study and seek permission to share their contact details with the study team.

### Eligibility criteria

Inclusion and exclusion criteria are reported in table 1. No recruitment quotas will be imposed, with respect to any participant characteristics. To reduce the risk of participant selection bias, all eligible young people will be invited to participate until the recruitment target is met.

**Table 1 T1:** Eligibility criteria

Inclusion criteria	Identified via SLaM’s C4C patient research participation register or referral to the study team by their clinician.
	Aged 13–25 years old at the time of study approach.
	Accessed mental health services at SLaM in the last 12 months.
	Has capacity to consent (and an adult with parental responsibility for young people aged 13–15 years old). Mental capacity will be assumed unless evidence from a clinician or during contact with the study team suggests otherwise.
Exclusion criteria	Unable to complete the questionnaires via the study software application or online survey platform.
	Admitted to an inpatient psychiatric ward, sectioned under the Mental Health Act or in prison at the time of approach.
	Clinician advises it is not appropriate to approach.

C4C, Consent for Contact; SLaM, South London and Maudsley NHS Foundation Trust.

### Sample size calculation

In a recent national community survey, the reported annual age-sex incidence of self-harm for young people aged 16–18 years old was 36.4% (95% CI 22.4 to 52.2) for men and 43.5% (95% CI 35.5 to 51.7) for women.^3^ Based on uptake of SLaM C4C patient research participation register, we estimate that if 600 young people consent to take part, 480 will be followed up during a 6-month period, resulting in at least 150 with an episode of self-harm. Using the most conservative estimates, if approximately 22.5% of those who do not display characteristic problematic patterns of social media usage (or smartphone usage) have an episode of self-harm and this increases to 35% in those identified with problematic usage in the previous week, we expect 86% power to detect a 12.5% increase in self-harm at 5% significance, assuming 480 young people are followed up.

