**Figure 1 F1:**
[figure not shown]
Participant flowchart.

Participants will then instal the study software application on their smartphone device and complete the baseline questionnaires. The study software application has been designed to continuously extract smartphone metadata and to deliver the questionnaires for the follow-up period (up to 6 months, reduced from 12 months following an initial pilot phase). Tables 2 and 3 outline data collection measures over the 6-month follow-up period related to primary and secondary objectives and other measurements. Participants who choose not to provide smartphone metadata (or use the study software application for any other reason) will be provided with a unique link to an online survey platform—Qualtrics (https://www.qualtrics.com)—to complete the questionnaires according to the same schedule. Participants will receive a reminder (an automated push notification and/or a prescheduled standardised text message and/or email) on the day a questionnaire is due, followed by a second reminder 7 days later if incomplete. The final set of questionnaires may also be sent via post. Participants who consent to provide their social media data will be contacted at baseline, months 3 and 6 to ask them to upload data. Participants will be given detailed guidance on how to request their data from the platforms and upload it to the study website via a unique link. Participants will receive a £10 voucher as a thank you for enrolling in the study, followed by £5 per month of continued participation and an additional £10 voucher for uploading their social media data at month 6.

**Table 2 T2:** Outline of data collection measures over the 6-month follow-up period related to primary objectives

Measure	Description	Data collected at:						
		Baseline	Month 1	Month 2	Month 3	Month 4	Month 5	Month 6
Socio-demographic questionnaire	Including age, gender, ethnicity, education and/or employment status, smoking, alcohol consumption and drug use.	X						
Child and Adolescent Self-harm in Europe (CASE) study criteria^48^	Occurrence and characteristics of historical and current (ie, in the last month) self-harm events will be collected using an adapted self-report version of the two-item CASE study criteria.^48^	X	X	X	X	X	X	X
Self-reported social media use	Including which social media platforms are used, types of activity (eg, to share something, or to comment on a post) and average duration of daily usage.	X						X

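### The 150 expected cases over 6 months rest only on annual community incidence, and do not follow from the risks that give 86% power

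*Protocol article*

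**What the plan says.** All the figures are in the protocol article, under Sample size calculation. The rates come from a single source, introduced as "In a recent national community survey" and described as "the reported annual age-sex incidence of self-harm" at ages 16 to 18: "36.4% (95% CI 22.4 to 52.2) for men and 43.5% (95% CI 35.5 to 51.7) for women".

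The section then assumes 600 consenting participants, of whom "480 will be followed up during a 6-month period, resulting in at least 150 with an episode of self-harm". For power, it supposes that "approximately 22.5% of those who do not display characteristic problematic patterns of social media usage (or smartphone usage) have an episode of self-harm" and that "this increases to 35% in those identified with problematic usage in the previous week". It calls these the most conservative estimates and states 86% power at 5% significance for the 12.5-point difference. It gives neither a time base for 22.5% and 35% nor the proportion of participants expected to be exposed.

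Under Recruitment method and study procedures, follow-up is given as "up to 6 months, reduced from 12 months following an initial pilot phase".

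**The concern.** Annual rates are followed directly by a 6-month case count, with no conversion and no 6-month or clinical-sample rate. The count fits the quoted rates over 12 months but not over 6, unless something further is assumed. The power inputs are also close to the lower confidence limits of the annual figures (22.4% and 35.5%), which raises the question of whether they are annual risks too.

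Self-harm events are the primary outcome, and the primary model estimates the relative risk of an episode. If the study yields fewer cases than stated, its power is lower than stated, and a null result would be read as stronger evidence of no association than it is.

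**Working it through.** **Inputs.** From Sample size calculation: 480 followed up; annual risks 36.4% (22.4 to 52.2) and 43.5% (35.5 to 51.7); at least 150 cases; 22.5% against 35%; 86% power; 5% significance. Assumed here because not stated: two-sided test, 240 exposed and 240 unexposed.

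**1. The plan's own power.** For a two-proportion z-test, power = Φ[(p1 − p0 − 1.96·SE0)/SE1], with SE0 from the pooled risk and SE1 from the separate risks. With p0 = 0.225, p1 = 0.35 and 240 per group, the pooled risk is 0.2875, SE0 = 0.0413 and SE1 = 0.0409. Power = Φ[(0.125 − 0.0810)/0.0409] = 85.9%. The stated 86% reproduces.

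**2. Cases from the cited rates over 12 months.** 480 × 0.364 = 175; 480 × 0.435 = 209. Both exceed 150.

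**3. Cases from the cited rates over 6 months.** Under a constant hazard, 6-month risk = 1 − √(1 − annual risk).
- Men's rate: 1 − √0.636 = 20.3%, and 480 × 0.2025 = 97 cases.
- Women's rate: 1 − √0.565 = 24.8%, and 480 × 0.2483 = 119 cases.
- Simple halving: 18.2% and 21.75%, or 87 and 104 cases.
- Lower confidence limits (constant hazard): 57 and 95 cases.
- Upper confidence limits (constant hazard): 148 and 146 cases.

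In reverse, 150/480 = 31.25% in 6 months, equivalent to 1 − 0.6875² = 52.7% a year.

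**4. Do the power inputs give 150 cases?** At 1:1, 240 × 0.225 + 240 × 0.35 = 54 + 84 = 138 cases. For 150 cases with x exposed, 480 × 0.225 + 0.125x = 150, so x = 42/0.125 = 336, which is 70% exposed. At 144 unexposed and 336 exposed, SE0 = 0.0462 and SE1 = 0.0435, and power = Φ[(0.125 − 0.0905)/0.0435] = 79%. No single exposure split gives both 150 cases and 86% power from these risks.

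**5. Are the inputs conservative?** If 22.5% and 35% are 6-month risks, at 1:1 they average 28.75%. That is 1 − 0.7125² = 49.2% a year under a constant hazard, above both annual point estimates.

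**6. Cases and power under each reading** (1:1, two-sided 5%).

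| Reading | 6-month risks | Cases | Power |
|---|---|---|---|
| 22.5%/35% are 6-month risks | 22.5% v 35% | 138 | 86% |
| 22.5%/35% are annual, constant hazard | 12.0% v 19.4% | 75 | 61% |
| 22.5%/35% are annual, halved | 11.25% v 17.5% | 69 | 50% |
| Overall risk 20.3%, risk ratio 0.35/0.225 = 1.56 | 15.8% v 24.7% | 97 | 67% |
| Overall risk 24.8%, risk ratio 1.56 | 19.4% v 30.2% | 119 | 78% |

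In the last two rows the unexposed risk is 2 × overall risk/(1 + 1.556), and the exposed risk is 1.556 times that.

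**The case against.** The strongest defence is that the community survey is a poor guide to this cohort. Participants are secondary-care patients aged 13 to 25, self-harm is asked about monthly, and clinician-recorded events are added, so a higher 6-month proportion is plausible. The article's Introduction also notes that repetition is common. When the same people repeat, the share with any episode in 6 months exceeds the constant-hazard value and may approach the annual share, so the possible range runs from 87–104 up to 175–209 cases and includes 150. This stands: 150 is not shown to be unattainable. A reader might infer that it is, because 52.7% a year exceeds both upper confidence limits, but the margin is only 0.5 to 1.0 percentage points and depends on the constant hazard. What the defence does not supply is a figure, since the section neither makes the argument nor quotes a clinical or 6-month rate.

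A reader might also infer that true power is 50% to 61%. The document does not establish this. It requires 22.5% and 35% to be annual, which is inferred only from their closeness to the lower confidence limits. Another reading fits 22.5% equally well: the mean of the two annual rates, 39.95%, converts to 22.5% over 6 months. Lower power also requires 35% to be rescaled; holding the 12.5-point difference above a 12.0% baseline gives about 95%.

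Nor can it be inferred that the calculation was left unrevised when follow-up was cut from 12 months. The section already refers to 6 months, and the full protocol is not shown.

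**Conclusion.** The point holds as a lack of support and an internal mismatch, not as an error in the power formula. The only cited rates are annual. They give about 97 to 119 cases in 480 over 6 months under a constant hazard, or 87 to 104 by halving, against the stated minimum of 150. Separately, and whatever the time base, the stated risks yield 138 cases at the equal split that reproduces 86% power; a split that yields 150 cases has about 79% power. This second result needs no assumption about the hazard, only a two-sided 5% test.

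If 22.5% and 35% are 6-month risks, 86% stands at 1:1 but has no cited basis, and describing the inputs as the most conservative is not supported against the quoted point estimates. If they are annual, power over 6 months is about 50% to 61% with both risks rescaled. The text does not settle which applies.

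**What to change.** In Sample size calculation, state the time base and source of 22.5%, 35% and 150, and the assumed exposure split. Then restate cases and power from one consistent set of 6-month risks, by one of these routes:

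- Quote the 6-month self-harm proportion from the pilot or the current cohort, pooled over exposure groups, and derive both figures from it.
- Convert the annual rates and keep cases and power matched. If 22.5% and 35% are annual: about 75 cases and 61% power (69 and 50% by halving). If the overall 6-month risk is 20.3% to 24.8% with a risk ratio of 1.56 and equal groups: 97 to 119 cases and about 67% to 78% power.
- If 22.5% and 35% are 6-month risks, cite their basis, keep 86% at 1:1, and change the case count to about 138.

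Justify or delete the description of the inputs as the most conservative. The cost is a wording change, and the stated figures will probably be less favourable. No extra participants are needed.
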